# Lay Summary

Twenty percent of breast cancer survivors have insomnia, which is defined as persistent trouble falling and/or staying asleep that results in difficulty functioning during the day. Sleep difficulties often begin at cancer diagnosis, become worse during cancer treatment, and continue into cancer survivorship. Insomnia interferes with daily activities and may cause other mental and physical health problems. It also makes it more difficult to cope with cancer treatment and makes recovery more challenging. For these reasons, it is important to address early signs of sleep problems in cancer patients by offering interventions that may prevent the development of insomnia. Sleep Restriction Therapy is one such intervention, which helps improve night-time sleep by stabilising sleep patterns and reducing time spent in bed awake. Sleep Restriction Therapy has been used successfully to treat chronic insomnia in breast cancer survivors who have completed cancer treatment. However, it has never been tested on newly diagnosed breast cancer patients with early signs of sleep disturbance, who are undergoing cancer treatment. This study will address this knowledge gap by randomly assigning newly diagnosed patients with poor sleep to receive either Sleep Restriction Therapy or a sleep hygiene education control intervention. We will assess sleep and mental health before and after both interventions to determine how feasible and acceptable Sleep Restriction Therapy is to patients and to plan for a future, larger study. Throughout, we will work with patients with lived experience of breast cancer and poor sleep to ensure our study is informed by their expertise.

# Background

Insomnia disorder (ID) is a causal factor in the evolution and maintenance of physical and mental ill health ([1](#_ENREF_1)), a robust risk factor for all-cause mortality ([2](#_ENREF_2)), and the most commonly reported mental health complaint amongst cancer populations ([3](#_ENREF_3), [4](#_ENREF_4)). Breast cancer patients report the highest rate of ID (~40%) and more circadian disruption than other cancer groups ([3](#_ENREF_3)), which is associated with significantly shorter overall cancer survival, independent of other prognostic factors ([5](#_ENREF_5)). For these reasons, this study aims to explore the feasibility of providing an early sleep intervention to avert the development of ID in breast cancer patients.

Two recent reviews ([5](#_ENREF_5), [6](#_ENREF_6)) synthesise models of insomnia development, the most well-cited of which is Spielman’s diathesis-stress model (1987). This model explains how the stress of cancer diagnosis precipitates the onset of acute insomnia, then altered rest/activity rhythms (i.e., daytime napping, time in-bed extension), implemented to combat the impact of acute insomnia, perpetuate its transition to ID ([7](#_ENREF_7)). Our group have previously completed a programme of work exploring this model of insomnia aetiology in breast cancer ([8](#_ENREF_8), [9](#_ENREF_9), [10](#_ENREF_10), [11](#_ENREF_11)). We reported that 46% of newly diagnosed breast cancer patients develop acute insomnia following diagnosis ([8](#_ENREF_8)). Rates of insomnia remain stable and pervasive for at least 12-months post-diagnosis, indicating that acute insomnia develops a chronic course if not addressed ([8](#_ENREF_8), [11](#_ENREF_11)). We also found that breast cancer patients attempt to compensate for the impact of acute insomnia by engaging in behaviours known to promote the development of ID ([9](#_ENREF_9)). Finally, we reported that ID has a significant negative impact on the psychological and physical wellbeing of people with breast cancer ([10](#_ENREF_10)). Therefore, breast cancer patients would benefit from an early intervention that targets acute sleep disturbance.

Sleep Restriction Therapy (SRT) is an established, single-component treatment for ID and a key ingredient within multicomponent Cognitive Behavioural Therapy for insomnia (CBT-I) ([12](#_ENREF_12)). SRT targets altered rest/activity rhythms, with the aim of increasing homeostatic sleep pressure, over-riding cognitive and physiological arousal, and strengthening circadian control of sleep ([12](#_ENREF_12)). This is because sleep extension leads to a disparity between sleep opportunity and sleep ability, alters the regularity of the sleep-wake schedule, and consequently, increases exposure to light, the chief zeitgeber for the circadian clock. Therefore, whilst SRT may be particularly useful for breast cancer patients with acute insomnia, there are no efficacy studies of SRT in the breast cancer patient population or the acute insomnia population.

One of the strengths of our approach is that it identifies patients with initial sleep disturbance who would benefit from early intervention to prevent insomnia progression. However, robust research is required to evaluate whether SRT is tolerable for newly diagnosed breast cancer patients at such a challenging time. Typically, cancer patients undergoing active treatment are excluded from sleep research studies, so their ability to commit during a time of high psychological impact is unclear. Reassuringly, our Public and Patient Involvement (PPI) group strongly endorse our research plans, and the importance of offering SRT during the acute cancer treatment phase, not least because of the potential for prevention of ID. Finally, assessing intervention acceptability will provide insight into potential optimisation of SRT and recommendations for enhancing future scalability and translation within healthcare. This study will identify and resolve these key areas of uncertainty, informing the design of a larger randomised controlled trial (RCT) and minimise barriers to wider-scale adoption of SRT within cancer care settings.

# Preparatory Research

We have established a sleep and cancer research programme focusing on the aetiology, impact, and non-pharmacological management of insomnia in breast cancer patients. Our research programme has enabled the development of an international breast cancer research register (n=879) and PPI network. Informed by this network, our next step is to evaluate whether we can prevent the development of ID in this at-risk population by offering an early, evidence-based insomnia intervention that targets acute sleep disturbance. Treating acute insomnia has been identified as a priority issue by a task force of experts from the World Sleep Society in their recent guideline for the diagnosis and treatment of insomnia ([13](#_ENREF_13)). Our preparatory pilot work, comprising systematic literature reviews, qualitative studies, observational analyses, RCTs and public engagement work, all validate the proposed study. We recently demonstrated that exhibiting acute sleep disturbance in response to breast cancer diagnosis results in a six-fold increase in insomnia prevalence ([8](#_ENREF_8)) and is a risk factor for the development of ID ([11](#_ENREF_11)). We have also demonstrated that ID is deleterious for psychological and physical wellbeing in breast cancer patients ([10](#_ENREF_10), [14](#_ENREF_14)). Our qualitative studies ([9](#_ENREF_9), [10](#_ENREF_10)) reveal that breast cancer patients implement sleep extension behaviours, intended to compensate for sleep loss, that increase their risk of ID. SRT is an established treatment for ID that works by addressing these sleep extension behaviours to stabilise the sleep-wake schedule. A recent meta-analysis of RCTs by our team demonstrates that SRT significantly improves insomnia severity and sleep continuity in patients with ID ([12](#_ENREF_12)). Therefore, it offers promise as an early therapeutic approach for acute insomnia. Our data also show that insomnia interventions (such as SRT) improve concomitant symptoms like anxiety, depression, and fatigue in breast cancer patients ([14](#_ENREF_14), [15](#_ENREF_15)). In addition, because SRT leads to reduced sleep variability and improved sleep consolidation and quality, it may minimise these other prevalent cancer-related side effects as they emerge, so sleep is a promising transdiagnostic therapeutic target for wellbeing more generally. However, no research has evaluated SRT for acute insomnia in cancer patients, so it is unclear whether it is tolerable and efficacious for patients undergoing cancer treatment.

# Aims

The primary aim of this project is to assess the feasibility and inform the design of a full-scale RCT of SRT for newly diagnosed breast cancer patients with acute insomnia. Secondary aims of this project are to assess the effects of SRT alongside a sleep hygiene education (SHE) control on sleep, rest-activity rhythms, and mental health.

# Study Objectives:

1. To determine rates of participant recruitment and retention
2. To determine intervention fidelity
3. To determine outcome measure completion
4. To determine intervention acceptability

We wish to formally consider issues of recruitment and retention, fidelity, completion of outcome measures, and acceptability, to inform the future development of a definitive multi-centre RCT. Our success criteria for moving forward to full trial are based on a similar pilot RCT of breast cancer patients with insomnia ([16](#_ENREF_16)) and a RCT of Sleep Restriction Therapy in primary care ([17](#_ENREF_17)).

Table 1. Overview of objectives and success criteria

| **Objective** | **Quantitative success criteria** | **Quantitative measurement** | **Timepoint(s) of evaluation** | **Qualitative insights (evaluated throughout)** |
| --- | --- | --- | --- | --- |
| **Recruitment and retention rates** | Recruitment - 80% of target achieved | Enrolment logs for all consenting patients. Pre-screen failure logs for patients who meet inclusion criteria but are not enrolled | Screening | Understanding trial implementation and participation / offer of uptake |
|  | Retention -  <30% attrition rate | Completion of outcome measures | 12 weeks post randomisation |  |
| **Intervention fidelity** | Therapist adherence - >70% of SRT elements covered during sampled sessions | Independent clinician review of recorded SRT sessions and  completion of fidelity rating scale | 6 weeks post randomisation | Understanding therapist and patient perspectives on delivery and receipt of SRT sessions |
|  | Patient engagement -attendance at 2/4 SRT sessions | Intervention attendance logs | During intervention phase |  |
|  | Control group contamination - <10% of SHE patients receive SRT through nurse therapist | Client Service  Receipt Inventory | 6 weeks and 12 weeks post randomisation |  |
| **Outcome measure completion** | >70% of questionnaires fully completed | Completion of outcome measures | Baseline, 6 weeks and 12 weeks post randomisation | Explore the acceptability of the outcome measures for clinicians and patients |
| **Intervention acceptability** |  |  |  | Exploration of cancer journey, service ecology, role of early insomnia intervention and experiences of SRT or SHE. |

# Study Design

A pilot, two-centre, two-arm, parallel group, block randomised (1:1) controlled trial will compare SRT with a SHE control. Both groups will continue to receive standard breast cancer treatment as usual (TAU). Consistent with the requirements of a pragmatic trial, there will be no limitations upon usual care for either group. In this way, the trial represents a comparison of SRT+SHE (+TAU) vs. SHE (+TAU), permitting clear judgements to be made regarding the relative clinical utility of SRT. Due to the nature of the SRT intervention, the therapist and patients cannot be blinded to treatment allocation. However, the statistician will be blinded to treatment allocation (i.e., SRT or SHE) until after analysis is complete.

# Participants

Our target population is newly diagnosed, non-metastatic patients whose primary cancer treatment is surgery. Main study exclusion criteria are limited to conditions contraindicated for SRT or factors that would preclude implementation of SRT. SRT is contraindicated in people with dementia / mild cognitive impairment, epilepsy and psychosis because these conditions can be exacerbated by sleep deprivation, which is a common side effect of SRT. If it becomes clear that a participant has lost capacity during the study, they will be withdrawn from the study but any data they have contributed will be retained and used in the analyses.

- 1. Inclusion Criteria

1. Participant is willing and able to give informed consent
2. Aged 18 years and above
3. Screen positive for acute insomnia, defined as dissatisfaction with sleep quality or duration, accompanied by other night / daytime symptoms, present for between 2 weeks and 3 months
4. Newly diagnosed with non-metastatic breast cancer
5. Primary cancer treatment is surgery
   1. Exclusion Criteria:
6. Pregnancy
7. Additional sleep disorder diagnosis (e.g., restless legs syndrome, obstructive sleep apnoea, narcolepsy) or screen “positive” for additional sleep disorder at study screening interview
8. Dementia / Mild Cognitive Impairment
9. Epilepsy
10. Psychosis (schizophrenia, bipolar disorder)
11. Current suicidal ideation with intent or attempted suicide within past 2 months
12. Night, evening, early morning, or rotating shiftwork
13. Current / previous psychological treatment for insomnia during the last 12 months
14. Chemotherapy and/or radiotherapy commenced

# Procedures

- 1. Patient Screening and Recruitment

Adults will be recruited consecutively from breast cancer results clinics in NHS Greater Glasgow and Clyde and NHS Grampian. Our target population is newly diagnosed, non-metastatic patients whose primary cancer treatment is surgery. Participants can be recruited into the study at any point between cancer diagnosis and the onset of chemo / radiotherapy. Potentially eligible patients will be identified by surgical teams at the breast cancer results consultation. The breast cancer research nurse will inform potentially eligible patients about the study, and if they are interested in participating, they will take the patient through a brief screening questionnaire to confirm initial eligibility (e.g., sleep status, age, not currently pregnant). We have included this brief screening questionnaire prior to signing the consent form based on feedback from our PPI representatives. They felt it was unnecessary (and burdensome) to read the participant information sheet, only to then be excluded by simple criteria that could easily and quickly be assessed early in the study (e.g., current pregnancy). Since patients are not enrolled in the study until they sign the consent form, any data provided until this point will be deleted.

If patients do meet the first set of inclusion criteria, the nurse will pass their contact details on to the research team. The study researcher will then contact the patient to discuss the trial in more detail, offering an opportunity for questions to be asked and answered. If potentially eligible patients express willingness to participate, they will be sent an online participant information sheet and consent form. To ensure we engage with people for whom the study may be both relevant and suitable, the main study exclusion criteria will be very clear in the participant information sheet. If interested in participating, the patient will be required to electronically sign the consent form, marking enrolment into the study, and the second stage of screening will commence.

The second stage of screening involves the completion of a semi-structured interview (on Qualtircs or administered by the researcher over Zoom/Teams or telephone) to establish full study eligibility. This includes assessment of current sleep status (based on diagnostic criteria for acute insomnia outlined in 6.1 above), current psychiatric symptoms and review of other relevant medical information (diagnosis of other sleep disorders, other medical and psychiatric disorders). This is to confirm the diagnosis of acute insomnia and establish that there are no medical or psychiatric conditions that might preclude someone from taking part in the study. During screening, we will also give each participant the opportunity to sign a health release form. This will give us permission to contact their health care provider of choice (e.g., their GP) with information that has been uncovered as part of their participation in this study (and only this information e.g., uncovering potential Major Depressive Disorder), that might warrant further follow-up but that cannot be provided as part of this trial. This will be an opt-in opportunity, and not signing the health release form will not have any impact on their participation in the study. In cases where the participant discloses suicidal ideation or physical/sexual abuse to them or others, the respective authorities will be contacted by the CI even if consent for this action is not provided by the participant. This is made clear to the participant in the participant information sheet and also verbally prior to screening. Once eligibility is ascertained, patients will be randomly assigned to SRT or the SHE control group.

- 1. Randomisation

We aim to randomise 40 patients (n=20 in each trial arm), and conservatively estimate that we will recruit 5 patients per month across both sites in a 10-month recruitment window (assuming a dropout rate of 20%). This represents <10% of the total number of patients seen per month in these clinics. NHS Greater Glasgow and Clyde and NHS Grampian serve a combined population of around 1.7M. In the NHS GGC South Sector breast service, based at Gartnavel General Hospital, there are 550 new breast cancers each year, with over 60% of this population undergoing surgery as their primary treatment. In NHS Grampian, 545 new breast cancers (screening and symptomatic pathways) were diagnosed in 2021. About 84% of these newly diagnosed patients received surgery as their primary treatment. Of these, we conservatively estimate that 40% will meet criteria for acute insomnia (n=315). From these, we aim to randomise patients to take part in the study.

- 1. Study Assessment Points

After randomisation to SRT or SHE, patients will be sent an email with a link to complete a baseline (pre-intervention) assessment of sleep, fatigue, and mental health (questionnaires can be completed over the telephone or on paper should the participant prefer this). Patients will also be required to complete the consensus sleep diary and wear an actigraphy device for 7 days prior to commencement of SRT/SHE to record sleep and rest/activity rhythms. Within-treatment session outcomes for SRT will also be explored using sleep diaries and actigraphy. After completion of the baseline assessment, patients will either be referred to the nurse therapist for commencement of the SRT protocol or provided with the SHE resource. At 6 weeks, and 12 weeks post-randomisation, patients will be requested to complete the same battery of questionnaires as during the baseline assessment. Following completion of the final study assessment (12 weeks post-randomisation), those randomised to the SHE condition will be offered the opportunity to complete the SRT protocol without the requirement to complete any further assessments.

- 1. Primary and Secondary Outcomes

As this is a feasibility study, our primary outcome relates to issues of recruitment and retention, fidelity, completion of outcome measures, and acceptability. Quantitative and qualitative measurement of each of these primary outcomes are detailed in table 1 (section 5) above. Our secondary outcomes relate to improvement in sleep, circadian rhythm, and mental health following SRT. We will evaluate improvements in insomnia severity at 6 weeks and 12 weeks, assessed by the Insomnia Severity Index (ISI), which is valid and sensitive to change in insomnia severity in cancer patients. We will also analyse improvements in mental health [depression (PHQ-9); anxiety (GAD-7)], rest-activity rhythms [fatigue (FACT-F); actigraphy] and estimates of subjective sleep (Sleep Diary). We will also collect EQ-5D-5L data to measure health-related quality of life, from which quality adjusted life years (QALYs) can be calculated.

- 1. Assessment Tools

1. *Insomnia Severity Index (ISI):* The ISI is a brief 7-item scale that measures insomnia severity. It has adequate internal consistency with evidence supporting concurrent, predictive, and content validity.
2. *Patient Health Questionnaire 9 (PHQ-9):* The PHQ-9 is a self-administered screening tool for assessment of the severity of depressive symptoms. The questionnaire has good reliability and validity. It is a simple, brief and reliable tool for the screening and evaluation of depression.
3. *Generalised Anxiety Disorders 7 (GAD-7):* The GAD-7 is a brief and reliable scale that measures the severity of anxiety symptoms. It is appropriate for use with cancer patients and has good reliability and validity.
4. *):* The FACT-F is questionnaire designed to assess fatigue in people with cancer, with good reliability and validity data.
5. *EQ-5D-5L:* This scale is a validated measure of health-related quality of life, from which quality adjusted life years (QUALY) can be obtained. One of the aims of a future definitive RCT will be to include a cost-utility evaluation, therefore we would like to collect some preliminary data now to determine effect sizes for a full-scale RCT.
6. *Consensus Sleep Diary:* Prospective daily diary entries will be used to assess self-reported sleep patterns over a 7-day period. Sleep diaries are a reliable and valid index of insomnia and have been used as an outcome measure in efficacy studies on insomnia. During the baseline, intervention, 6 week and 12 week assessment, prospective self-report data will be collected using the consensus sleep diary. This consists of an assessment of bedtime, sleep onset latency, wake time after sleep onset, rise time, total sleep time, ratings of sleep quality and napping behaviour.
7. *Actigraphy:* The actigraphy device is a wristwatch like device that measures activity through an accelerometer (motion sensor that records the occurrence and degree of motion). Reduced activity can be used as a proxy for sleep, thus providing information about the sleep-wake cycle.
8. *The Client Service Receipt Inventory (CSRI):* The CSRI is a research tool that collects information on service utilisation, income, accommodation and other cost-related variables.
9. *Patient Satisfaction with Treatment:* An adapted version of the Patient Satisfaction Questionnaire Short Form (PSQSF) will be used to assess patient’s treatment satisfaction with the intervention.
10. *Safety:* Adverse events unrelated and related to the interventions will be recorded during treatment. A side-effects inventory, which was developed for individuals with insomnia undergoing behavioural treatments, will be used. Serious adverse events such as deaths, suicide attempts, and serious accidents will also be recorded. We will also encourage patients to contact us with any changes to their health and wellbeing.

Table 2: Overview of scheduled study assessments

| **Measures** | **Screening** | **Baseline (T0)** | **During SRT** | **6 weeks post-randomisation** | **12 weeks post-randomisation** |
| --- | --- | --- | --- | --- | --- |
| ISI, PHQ-9, GAD-7, FACT-F, |  | X |  | X | X |
| Sleep diary |  | 7 days | Daily | 7 days | 7 days |
| Actigraphy |  | 7 days |  | 7 days | 7 days |
| Enrolment logs (recruitment) | X |  |  |  |  |
| Fidelity rating scale (therapist adherence) |  |  |  | X |  |
| Intervention attendance logs (patient engagement) |  |  | X |  |  |
| Client Service Receipt Inventory (control group contamination) |  |  |  | X | X |
| Adverse Events |  |  | X | X | X |
| Treatment Satisfaction |  |  |  | X |  |
| Exit interviews (intervention acceptability) |  |  |  | X |  |

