# Data Analysis

As this is a pilot study, interpretation of the results will be considered with reference to the MRC Framework for Complex Interventions. As they relate to feasibility, no formal sample size calculation has been performed for our primary aim. Details of patient screening, recruitment, retention, withdrawal, adherence, acceptability and follow-up will be reported descriptively as outlined in table 1 above. Success criteria for these domains are summarised as follows: recruitment – 80% of target achieved; retention - <30% attrition; therapist adherence - >70% of SRT elements covered; patient engagement - attendance at 2/4 SRT sessions; control group contamination - <10% of SHE patients receive SRT; outcome measure completion - >70% of questionnaires fully completed.

To fulfil our secondary aim, between group comparisons of ISI 6-weeks post-randomisation will be done using t-tests or Mann-Whitney tests. Based on a mean difference in ISI of 4.2 between groups ([12](#_ENREF_12)) and an estimated standard deviation of 4.5 ([17](#_ENREF_17)) a sample size of 20 in each arm is required to achieve a power of 80% with a 5% significance level (we will aim to recruit 25 patients to each arm of the trial to accommodate our assumed dropout rate of 20%). The results from this feasibility RCT will help to refine the sample size calculation for a future definitive RCT.

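### The protocol gives two sample targets, 40 randomised or 50 allocated; at its own 20% dropout only 50 reaches the stated power, and the recruitment pass mark is either 32 or 40

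*Protocol*

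**What the plan says.** Two sections of the protocol state a target.

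- **Procedures, Randomisation:** "We aim to randomise 40 patients (n=20 in each trial arm"). The same sentence forecasts that "we will recruit 5 patients per month across both sites in a 10-month recruitment window (assuming a dropout rate of 20" per cent).
- **Data Analysis:** 20 per arm is the number required for 80% power at the 5% level in the 6-week ISI comparison, and "we will aim to recruit 25 patients to each arm of the trial to accommodate our assumed dropout rate of 20" per cent.

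The inputs to the power calculation are "Based on a mean difference in ISI of 4.2 between groups" and "an estimated standard deviation of 4.5". The test is a t-test or a Mann-Whitney test.

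The first success criterion in Table 1 (Study Objectives) is "Recruitment - 80% of target achieved". Data Analysis repeats it, and neither place gives the target as a number. Table 1 names the data source as "Enrolment logs for all consenting patients", together with logs of pre-screen failures, and sets the evaluation at screening. Under Patient Screening and Recruitment, signing the consent form is described as "marking enrolment into the study, and the second stage of screening will commence". Randomisation follows only once that second stage has confirmed eligibility.

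**The concern.** A patient belongs to an arm only after allocation, so 25 in each arm means 50 randomised. The Randomisation section says 40. Nothing in the protocol reconciles the two figures, and two things depend on which one applies.

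1. **Power for the secondary aim.** If 40 are randomised and the protocol's own dropout occurs, fewer patients are analysed than the calculation requires.
2. **The recruitment criterion.** Recruitment is one of the primary feasibility outcomes and the first criterion for moving to a full trial. A percentage of an unspecified target can be read either way once the final count is known. It is also unclear whether the numerator is people who consented or people who were randomised.

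**Working it through.** **Inputs.** From Data Analysis: difference 4.2, SD 4.5, power 80%, significance level 5%, dropout 20%. From Study Design: 1:1 allocation. Sidedness is not stated. Two-sided is assumed, because a one-sided test would need only 15 per arm and would not reproduce the protocol's 20.

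**Step 1: reproduce the protocol's figure.**
- Standardised difference: d = 4.2 / 4.5 = 0.933.
- Normal approximation: n = 2 × (1.960 + 0.842)² / d² = 15.70 / 0.871 = 18.02, so 19 per arm.
- Exact two-sample t-test (noncentral t with 2n − 2 degrees of freedom and noncentrality d × √(n/2)): n = 19.03, so 20 per arm.
- Mann-Whitney, with relative efficiency 0.955 for normal data: 19.03 / 0.955 = 19.9, so 20 per arm.
- Inflation for dropout: 20 / (1 − 0.20) = 25 per arm, 50 in total.

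Both the 20 and the 25 reproduce. The 20 is therefore the number per arm needed with 6-week ISI data, and the 25 is the number per arm to randomise.

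**Step 2: check the forecast in the Randomisation section.** 5 per month × 10 months = 50, and 50 × 0.80 = 40. The forecast follows the same path from 50 to 40 as Data Analysis. The 40 fits as the number retained, not the number randomised.

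**Step 3: power under each stated target at 20% dropout.**

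| Randomised | Analysed per arm | t-test power | Mann-Whitney power |
| --- | --- | --- | --- |
| 50 | 25 × 0.80 = 20 | 82.0% | about 80% |
| 40 | 20 × 0.80 = 16 | 72.4% | about 70% |

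The Mann-Whitney figures use the 0.955 efficiency. Simulation with normal data gave 80.0% at 20 per arm and 69.4% at 16.

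**Step 4: the recruitment pass mark.**
- Target 40: 0.80 × 40 = 32.
- Target 50: 0.80 × 50 = 40.

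A final count of 32 to 39 passes on the first target and fails on the second. The two pass marks differ by 8 patients.

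**Step 5: what is counted.** The order of events is consent (which is enrolment), second-stage screening, then randomisation. Table 1 takes its data from logs of consenting patients, while the numerical target under Randomisation is in randomised patients. The two counts differ by the number who fail second-stage screening, which the protocol does not estimate.

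**The case against.** The strongest reply is that there is really one plan. The forecast and Data Analysis both run from 50 to 40, and the fault may be a single verb, with randomise written where retain was meant. That is probably right, and it means the sample size arithmetic is sound. It does not remove the conflict, because the sentence as it stands sets the number to randomise at 40.

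A second reply is that 50 consent and 40 are randomised after losses. This fails on two counts. Data Analysis places 25 in each arm, which is after allocation. And if the 20% were lost before randomisation, nothing would cover losses between randomisation and the 6-week ISI.

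It is also fair to say that the ISI comparison serves a secondary aim of a pilot, so a drop of about 10 points in power is not grave in itself. That stands. The recruitment criterion is the weightier part.

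A reader might infer more than the protocol supports on four points:

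- **That 80% power is reached only with 50 randomised.** With no dropout, 40 randomised would give 82%. At 20% dropout, 48 randomised (24 × 0.80 = 19.2, about 19 per arm) would give about 80%. The statement holds only between the two stated targets at the stated dropout.
- **That power would be lower still if recruitment stopped at the pass mark of 32.** This adds under-recruitment, which lowers power in any trial and is not caused by the contradiction. The 80% criterion governs progression to a full trial; it is not a planned sample size.
- **That people screened out after consent count towards success.** Table 1 names a data source and states no such rule. It leaves the numerator unclear, no more.
- **That randomising 50 needs no one beyond the forecast.** If the 5 per month are counted at consent, second-stage screen failures would leave fewer than 50 to randomise.

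**Conclusion.** The inconsistency is real and should be corrected. Of the two stated targets, only 50 randomised reaches the stated power under the protocol's 20% dropout: about 82%, against about 72% with 40 randomised (about 80% and 70% for Mann-Whitney). These figures rest on the protocol's difference and SD, equal loss in the two arms and a two-sided 5% test; the Mann-Whitney figures also assume normal data.

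The larger consequence is that a primary feasibility outcome has two possible pass marks, 32 and 40. The ambiguity changes the decision only if the final count falls between 32 and 39. Outside that range both targets give the same answer, provided it is settled who is counted.

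**What to change.** Use one target in Study Objectives (Table 1), Randomisation and Data Analysis. There are two ways to do this:

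- **Randomise 50:** state that 50 (25 per arm) will be randomised in order to retain 40 (20 per arm) at 6 weeks. The power statement then stands.
- **Randomise 40:** keep the present number and restate power as about 72% after 20% dropout.

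In either case, write the recruitment criterion as a count of randomised patients within the 10-month window: at least 40 of 50, or at least 32 of 40. Say also whether the forecast of 5 per month counts consents or randomisations.

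The cost is wording in three places, or a less favourable power figure. If the forecast counts consents, randomising 50 would need somewhat more than 50 consents. In that case, restating the power is the cheaper option.
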